### Randomization, blinding and treatment allocation

After inclusion, participants are randomly assigned to either the intervention group I-Sleep (before the start of the usual care) or the control group (usual care alone) on a 1:1 ratio. Variable block sizes are used. Randomization takes place at the patient level and is stratified by mental health outpatient clinics for mood disorders. An independent researcher has created an allocation scheme using a computerized random number generator (Castor). Randomization will be performed by another independent research assistant who reveals the randomization outcome. Due to the nature of the intervention, blinding of patients, therapists, researchers and research assistants was not possible.

### The investigational treatment: I-Sleep, CBT-I for insomnia

I-Sleep is a guided, internet-based treatment based on CBTi [22, 27, 28]. The I-Sleep program consists of five online sessions comprising text, videos, and exercises. Feedback on the exercises is provided by a trained therapist through the secured online platform. Online sessions are divided by subject addressing: 1) psychoeducation on normal sleep, sleep disorders, and sleep hygiene (i.e., behaviours that can promote or impede sleep), 2) sleep restriction (i.e., restricting time in bed to increase sleep pressure) and stimulus control (i.e., reinforcing the association of the bed with sleeping), 3) rumination and relaxation techniques, 4) cognitive restructuring (i.e., changing common misconceptions about sleep) and 5) relapse prevention. Patients need to monitor their sleep by filling out a sleep diary throughout the intervention and complete the exercises in the digital workbook. The therapy program takes less than 30 min a day. The total duration of the insomnia intervention is five weeks.

The intervention is provided in a blended format, comprising both face-to-face or videoconferencing sessions and online sessions. To promote compliance and establish a positive working relationship between the patient and therapist the first face-to-face (f-t-f) session is scheduled prior to the first online session. A second f-t-f session is scheduled after the second online session to provide additional support during sleep restrictions The third and final f-t-f session is scheduled upon completion of all online sessions. Following the I-Sleep intervention, all participants allocated to the intervention group will receive usual care for depression. Preferably both I-Sleep and the usual depression treatment will be delivered by the same therapist so that cognitive techniques introduced during I-Sleep may be worked through more quickly during depression treatment. However, this is not mandated by the study protocol.

I-Sleep is delivered through a secure web-based online treatment platform (Minddistrict, www.minddistrict.com). The platform is owned by a commercial stakeholder from which specialized mental healthcare outpatient clinics for mood disorders buy services. The internet platforms include a PC interface and mobile application providing patients access to I-Sleep, a digital workbook and a secure communication channel for both the therapists and patients.

All therapists involved will receive extensive training prior to their participation in the trial. Training comprises an online course (e-learning) and an interactive webinar providing information on the study design, insomnia in general, and the use of the I-Sleep program. Additionally, a manual describing various scenarios and suggestions for feedback based on possible response patterns of patients is available for trained therapists which can be used as a reference book. Upon completion of the I-Sleep training, bi-monthly Intervision sessions will be organised by experienced CBTi and I-Sleep therapists. Supervision is provided by a senior therapist. In addition, researchers and research assistants are available for questions and to provide technical support at any time for the duration of the trial.

### Usual care

All patients in this study will receive usual care for depression. Usual care is given according to the multidisciplinary Dutch guideline for depression care and contains (group) psychotherapy and/or antidepressant medication treatment. Therapy and medication use during the trial is monitored. Furthermore, therapists are requested to refrain from CBTi (particularly I-Sleep), but usual care is not restricted in any other way.

### Assessments

Measurements will be taken at baseline (T0) and at 3- (T1), 6- (T2), 9- (T3) and 12-month (T4) follow-up. All measures are completed online; participants will receive a link to the online questionnaires via email. Additionally, a randomly chosen selection of participants and therapists from all participating outpatient clinics for mood disorders will be invited for an in-depth interview by telephone as part of the RE-AIM process evaluation. Exit interviews will be held with participants who discontinue or deviate from intervention protocols. For a detailed overview of the measurements see Table 1.

**Table 1 Tab1:** Repeated measurements

Questionnaire	T0	T1	T2	T3	T4
Depression severity (PHQ-9)	x	x	x	x	x
Sleep quality (ISI)	x	x	x	x	x
Daily functioning (WSAS)	x	x	x	x	x
Quality of life (EQ-5D-5L)	x	x	x	x	x
Healthcare, patient and family costs (iMCQ)	x	x	x	x	x
Lost productivity costs (iPCQ)	x	x	x	x	x
Process evaluation questions	x	x			x

T0: baseline, T1: 3 months after T0, T2: 6 months after T0, T3: 9 months after T0, T4: 1 year after T0

Online measurements and instruments at different points of assessment. *PHQ-9* Patient Health Questionnaire-9, *ISI* Insomnia Severity Index, *WSAS* Work and Social Adjustment Scale, *EQ-5D-5L* EuroQol, *iMCQ* iMTA Medical Cost Questionnaire, *iPCQ* iMTA Productivity Cost Questionnaire, Process evaluation questionnaire according to RE-AIM framework adjusted to the EINSTEIN study

### Primary outcome: depression severity

The primary outcome is the change in depressive symptoms during one year of follow-up. Depressive symptoms will be assessed with the web-based Patient Health Questionnaire-9 (PHQ-9) at baseline and at 3, 6, 9 and 12 months of follow-up. The PHQ-9 scores each of the nine DSM criteria on a scale from "0" (not at all) to "3" (nearly every day), resulting in a total score ranging between 0 and 27 which is divided into increasing severity categories resulting in the PHQ Depression Severity Index [29]. Recent studies show that the PHQ-9 delivered using web-based technology is a reliable instrument to assess the severity and frequency of depressive symptoms in the previous two-week period [30, 31]

### Secondary outcomes

All secondary outcomes will be assessed online at the same measurement moments, at baseline, and at 3, 6, 9, and 12 months of follow-up using web-based questionnaires. Insomnia severity as measured with the Insomnia Severity Index (ISI) is a secondary endpoint. The ISI is a 7-item brief instrument that measures sleeping difficulties in the past two weeks, which has been validated for online use [32]. Each item is scored on a Likert scale from 0 to 4, comprising topics regarding sleeping patterns, interference with daily life and distress caused by an impaired sleeping pattern [32].

Daily functioning is assessed using the Work and Social Adjustment Scale (WSAS) which is a scale designed to measure functional impairment due to another cause or affliction [33].

General quality of life is measured using the five-level version of the EuroQol questionnaire (EQ-5D-5L) [34]. The EQ-5D-5L contains five dimensions (mobility, self-care, usual activities, pain/discomfort and anxiety/depression) that are rated using five levels (no problems, slight problems, moderate problems, severe problems and extreme problems) [34]. EQ-5D-5L health states will be converted to utility scores using the Dutch EQ-5D-5L tariff [35], which will then be used to calculate Quality-Adjusted Life-Years.

Costs will be measured from a societal perspective using web-based questionnaires based on the iMCQ and iPCQ. Cost categories that will be included are: 1) healthcare costs (primary and secondary care, complementary care and home care); 2) lost productivity costs (absenteeism from paid and unpaid work, and presenteeism); and 3) patient costs (informal care and other care services paid for by patients themselves). Valuation will be done according to Dutch costing guidelines [36]. For the valuation of health care utilization, lost productivity and informal care Dutch standard costs will be used. Medication use will be valued using prices of the Royal Dutch Society for Pharmacy. Patient and family costs other than informal care will be valued using self-reported prices. For the valuation of absenteeism from paid work, the friction cost approach will be used.

### Process evaluation

Parallel to the RCT, we will conduct a process evaluation using the RE-AIM model to investigate the Reach of different patient groups, Effectiveness on patients’ insomnia, Adoption of I-Sleep amongst therapists, Implementation of I-Sleep amongst therapists as well as fidelity of patients to the I-Sleep e-Health modules, and Maintenance of implementation by therapists [37]. For the development of the implementation plan, we will conduct several interviews with patients, therapists and managers from each mental healthcare outpatient clinic for mood disorders during and at the end of the study period. The interviews will also provide us with insight into facilitating and hindering factors as defined in the model of [38] for implementation and sustainable use of I-Sleep in practice, which can provide suggestions for improvements in the evidence-based multi-faceted strategy. The interviews will be recorded, anonymized and transcribed verbatim. The transcripts will be analysed according to standard methodology using thematic content analysis. In addition, a small number of process evaluation questions is added to the assessments at baseline, and at 3 (after the intervention period) and 12 months of follow-up. Table 2 provides an overview of the research objectives and data collection methods for the process evaluation using the RE-AIM framework.

**Table 2 Tab2:** Overview of research objectives and data collection methods RE-AIM

Quantitative methods					Qualitative methods			
Research objectives:	Baseline online questionnaire	T1 (3 month follow-up) online questionnaire	T4 (12-month folluw-up) online questionnaire	MindDistrictEPR (electronic patient record)	Exit Interview by telephone with patients opting out	Focus group and/or interviews patients (at T1)	Focus group and/or interviews therapists (at T1)	Interviews managers out patient clinics (at T1)
*Reach*								
1. Evaluating the procedures of recruiting Baseline	X					X	X	X
2. Determining reasons for joining, continuing with or opting out of the I-Sleep program among patients	X				X			
3. Determining patient characteristics e.g. demographics and mental health	X			X				
*Effectiveness*								
1. Evaluating the effect on the I-Slee program on insomnia and depression severity		X						
2. Evaluating the effect of the I-Sleep program among patients		X						
3. Determining satisfaction with the I-Sleep program and provided tools/guidance among therapists		X				X		
4. Determining satisfaction with the I-Sleep program therapists							X	
5. Determining satisfaction with the I-Sleep program and provided tools/guidance among outpatient clinic managers								X
*Adoption*								
1. Determining therapist characteristics e.g. demographics, skills and experience	X			X				
2. Evaluating the procedures of recruiting therapists	X			X			X	X
3. Determining reasons among therapists for joining, continuing with or opting out of using the I-Sleep program	X						X	
4. Evaluating the overall (starting) process of recruiting/adopting I-Sleep by the organisation								X
*Implementation*								
1. Determining treatment fidelity among patients, e.g. completed sessions and assignments		X				X		
2. Determining the degree in which the treatment protocol has been followed by therapists (fidelity and dosage)							X	
3. Determining the use (dosage and fidelity) of provided tools and guidance regarding the I-Sleep program among therapists							X	
*Maintenance*								
1. Evaluating the long-term effects and application of techniques from the I-Sleep program among patients			X					
2. Determining helpful elements in maintaining to apply techniques from the I-Sleep program among patients			X			X		
3. Evaluating the long-term use of the I-Sleep program among therapists							X	
4. Determining helpful elements in maintaining to use the I-Sleep program among therapists and in the outpatient clinic in general							X	X
5. Determining future activities and intention to use the program						X	X	X
*Overall*								
Determining the perceived barriers and facilitators to the adoption, implementation and continuations of the program						X	X	X

Measurements at different points of assessment according to the RE-AIM process evaluation principle for patients, therapists and outpatient managers. Where RE-AIM stands for: Reach, Effectiveness, Adoption, Implementation and Maintenance

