### Sample size

The sample size calculation is based on a previously conducted pilot study among depressive patients suffering from insomnia [24]. In this pilot study, the mean PHQ-9 score was 11.5 in the intervention condition (I-Sleep + usual care) and 15.0 in the control condition (usual care alone) at three months of follow-up. Assuming an SD of 7.1, an alpha of 0.05, and a power of 0.80, this results in a total required sample of 130. With four participating mental healthcare outpatient clinics for mood disorders and an Intraclass Correlation Coefficient (ICC) of 0.05, the total required sample size for the current trial is 140. Considering a dropout rate of 20% based on the pilot study, the required sample size is 175. This means all four mental healthcare outpatient clinics for mood disorders ought to include approximately 44 patients in total, i.e., 22 patients per year.

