### Statistical analysis

Statistical analyses will be performed according to the intention-to-treat principle and will include a head-to-head comparison of the intervention group with the usual care group. A priori, we decided on a subgroup analysis stratified for the use of sleep medication at baseline. Analyses will be (partly) conducted by two independent researchers to check the validity and correctness of the analyses and it will be documented which software is used over the course of this project.

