### Data management and quality assurance

The data of each participant will be stored in a case record form (CRF patient data file) on each study site. The CRF is available only to the research team on site and will not be disclosed to a third party. Participants in the EINSTEIN study will be pseudonymised, i.e., each participant will be identified by a four-digit number that contains no identifiable information. The master key connecting names to the code will be safeguarded by the principal investigators on each study site only. All data is collected digitally and de-identified using a four-digit code number via Castor, a certified online electronic data capture system for medical research. Except for the qualitative interviews with patients, therapists, and managers from each mental healthcare outpatient clinic for mood disorders during and at the end of the study period held for process evaluation purposes. Audio records of the interviews will be securely stored at the digital storage facilities of each participating location only for as long as it takes to transcribe the interview anonymously since we intend to publish the pseudonymised transcripts (instead of the audiotapes). Additionally, an administrative database will be used on each study site to ensure timely assessments and log any other relevant research activities. At the end of the trial, once collected, the anonymised interview transcripts, the de-identified baseline data, log files of the internet program, the de-identified database data, log files of research activities, and the follow-up data collected from all mental healthcare outpatient clinics will be stored safely at the Department of Research and Innovation of GGZ inGeest. All data will be processed, backed up periodically, and managed by the data management team of GGZ inGeest. Data will be handled confidentially complying with the General Data Protection Regulation (GDPR) and in accordance with the Dutch Medical Research Involving Human Subjects Act (WMO). Likewise, both Castor and the Minddistrict platform on which the I-Sleep intervention runs, comply with all the applicable laws and regulations, including ICH E6 Good Clinical Practice (GCP), 21 CFR Part 11, EU Annex 11, General Data Protection Regulation (GDPR), HIPAA (US), ISO 9001 and ISO 27001. Following a risk assessment of the EINSTEIN study, installing a data and safety monitoring board was deemed unnecessary considering it is not expected that the I-Sleep intervention in this study will cause additional harm or risk to participants. Documentation on the research project will be archived. Research data of the study will be stored and kept for fifteen years upon completion of the EINSTEIN trial and after the publication of the results, after which they will be destroyed.

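### Table 2 marks only self-report at three months as the source for I-Sleep completion, although it also lists the treatment platform as a data source

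*Protocol article*

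**What the plan says.** The Process evaluation section of the protocol article names "fidelity of patients to the I-Sleep e-Health modules" among the things to be investigated. Table 2 then assigns data sources to each objective. Under Implementation, the row "1. Determining treatment fidelity among patients, e.g. completed sessions and assignments" is marked for the T1 online questionnaire and for patient focus groups or interviews at T1, and for nothing else.

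The table also has a quantitative column headed "MindDistrictEPR (electronic patient record". It is marked for three rows: the Reach row "3. Determining patient characteristics e.g. demographics and mental health", and the Adoption rows on therapist characteristics and on recruiting therapists.

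Three other places bear on the point:

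- The section on the investigational treatment says that the five sessions are online, that the workbook is digital and on the platform, and that therapists give their feedback on exercises there.
- Data management and quality assurance lists "log files of the internet program" among the data stored at the end of the trial.
- Assessments says "Exit interviews will be held with participants who discontinue or deviate from intervention protocols".

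**The concern.** The number of sessions and assignments a patient has finished is something an online treatment platform would normally record. Table 2 takes it instead from patients' own accounts at three months. A questionnaire answered at T1 says nothing about those who do not answer, and patients who stopped I-Sleep may well be over-represented among them. Those who do answer rely on recall.

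Two uses of the figure are at stake. First, the Discussion explains that delivery was changed after the pilot: I-Sleep now precedes usual care instead of running alongside it, and it is guided. The investigators expect more patients to finish as a result. Checking that needs a completion rate with all patients randomised to I-Sleep as denominator. Second, if the trial shows no effect, the reader will want to know how much of the treatment was taken up.

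**Working it through.** The plan states no adherence figure, so there is none to reproduce. The check has two parts.

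**1. Reading the table.** Table 2 has eight source columns: baseline questionnaire, T1 questionnaire, T4 questionnaire, MindDistrict/EPR, exit interview, patient focus group or interview, therapist focus group or interview, manager interview. Matching the marks to the columns gives:

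- Patient fidelity (Implementation 1): T1 questionnaire; patient focus group or interview.
- Therapist fidelity and dosage, and use of tools (Implementation 2 and 3): therapist focus group or interview.
- MindDistrict/EPR column: Reach 3, Adoption 1 and Adoption 2 only.
- Exit interview column: Reach 2 only (reasons for joining, continuing or opting out).

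As printed, no Implementation objective draws on the platform. The marked sources cannot supply a rate for the whole I-Sleep arm: the questionnaire covers responders, and Assessments describes the interviewees as a random sample of participants.

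**2. How far a responder-only rate could be off.** Let d be the share of I-Sleep patients who do not answer at T1, r the completion rate among those who answer, and q the rate among those who do not. If answers are accurate, the reported rate is r and the true rate is (1 − d)r + dq. The overstatement is therefore

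r − [(1 − d)r + dq] = d(r − q).

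Inputs: d = 0.20 is borrowed from the Sample size section ("Considering a dropout rate of 20% based on the pilot study, the required sample size is 175"; 140 / 0.80 = 175). The plan does not say that this is T1 non-response in the I-Sleep arm, so its use here is an assumption. The values of r and q are also assumptions, with q set at zero, half of r, or equal to r.

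| r | q | true rate | overstatement |
|---|---|---|---|
| 50% | 0% | 40% | 10 points |
| 50% | 25% | 45% | 5 points |
| 50% | 50% | 50% | 0 |
| 70% | 0% | 56% | 14 points |
| 70% | 35% | 63% | 7 points |
| 70% | 70% | 70% | 0 |
| 90% | 0% | 72% | 18 points |
| 90% | 45% | 81% | 9 points |
| 90% | 90% | 90% | 0 |

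The range is 0 to 18 points. If q exceeded r, the sign would reverse: r = 50% and q = 70% gives 0.20 × (0.50 − 0.70) = −0.04, an understatement of 4 points. Inaccurate recall among responders would come on top, and the documents give no figure for it.

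**The case against.** Table 2 is an overview in a journal article, and an empty cell does not prove that the platform data will be ignored. Its marks are visibly not exhaustive. The row on the effect on insomnia and depression severity is marked for T1 only, although Table 1 collects PHQ-9 and ISI at every time point. One Effectiveness row names therapists but is marked for patient focus groups. The blank may be another slip, and the full protocol may name the logs. This stands as a caution about intent. It does not remove the point, because the article does name sources for this measure, and the correction is the same if the blank is a slip.

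Non-completers are also not invisible. Exit interviews are planned for them, and therapists can follow progress on the platform and at the final face-to-face session. That is true, but Table 2 uses exit interviews for reasons and not for fidelity, and neither route is set down as a count over the whole arm.

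Two stronger readings are tempting and are not supported:

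- A reader might infer that adherence will certainly be overstated. No section gives T1 non-response, an expected completion rate or the validity of the self-report. One can produce a reported 80% against a true 68% to 72% by assuming 20% to 40% completion among non-responders (0.8 × 0.8 + 0.2 × 0.2 = 0.68; 0.8 × 0.8 + 0.2 × 0.4 = 0.72), but the gap then comes from the chosen values.
- A reader might infer that a complete record of finished sessions is known to exist. The article mentions the program's log files without describing their content. That they show completion is a sound inference from sessions, workbook and feedback all being on the platform, but it is an inference.

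**Conclusion.** The point holds in a limited form. For a declared process aim, Table 2 names sources that depend on response and recall, and leaves empty the column for the platform on which the treatment runs. The completion rate may therefore be misstated, most plausibly upward if those who do not answer at T1 completed less. Under the assumptions shown, with non-responders completing no more than responders, the error lies between 0 and 18 points. The documents settle neither its size nor its direction.

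The consequence stays within the process evaluation and the interpretation of the result. "Statistical analyses will be performed according to the intention-to-treat principle", and no stated effectiveness analysis uses adherence, so a reader should not infer that the primary comparison is compromised. This is a minor but worthwhile improvement.

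**What to change.** In Table 2, mark the MindDistrict/EPR column for the patient fidelity row. State that completed sessions and assignments are counted from platform records for all patients randomised to I-Sleep, whether or not they answer at T1. Keep the T1 questionnaire, focus groups and interviews for reasons and experience.

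The cost is one mark in the table, one sentence and an export of log files already due to be stored. Before relying on them, the team should confirm that the logs record completion of sessions and assignments. If they do not, the therapists' feedback records on the platform are a possible substitute to check.
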